### Engagement and usage measures for iCBT

The log files on the online “Selfapy” platform will be utilized to keep track of certain data. These data include but are not limited to the number of times a subject visits the platform, the amount of time elapsed between logins and the amount of correspondence shared between a subject and his/her respective therapist. As an addendum, the platform’s track and change functionalities enable the collection of data on the subject’s exact amount of usage on the platform. This includes the frequency of visits to the online modules, how much time a subject spends on each module and the modules that have been completed by the subject and in which order. All the aforementioned information will provide an overall picture of the efficiency and success of the individual elements of the programme.

### Sample size

The between-group effect size estimate is based on meta-analytic evidence for the effect size observed in unaccompanied psychological interventions (*d* = 0.28) [16]. Treatment effect sizes in a sample with mild to moderately depressed subjects may be quite low. We conservatively reduced the estimated effect size to *d* = 0.23 [33].

Based on this effect size, a power of 0.80 and an alpha level of 0.05, we need a total of 200 subjects to address our hypotheses. The sample size was further estimated based on an expected drop-out rate of 50%. Drop-out rates in previous studies that used similar interventions ranged between 9% [9, 10] and 50% [34]. Based on this assumption, we would need a total of 400 subjects. The sample size was calculated using G-Power [35]. In addition, a comparison will be drawn between the unaccompanied and the accompanied versions of the online programme. The previously expanded experimental groups are compared to a control group, resulting in a total of three study groups to which the subjects are randomly assigned in a ratio of 2:2:1 (accompanied group: *n* = 160, unaccompanied group: *n* = 160, control group: *n* = 80).

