### Trial objectives

With this trial, we evaluate the efficacy of the online self-help programme “Selfapy” and deduced the following hypotheses. The framework of the trial is superiority. The Becks Depression Inventory - II (BDI-II) [21] thereby serves as the primary outcome measure and assesses the depressive symptomatology.

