### Planned statistical analysis

The recorded data of the different measurement times (T1, T2, T3 and T4) for both intervention groups and the control group are analysed. The treatment results of all subjects (pre-post difference) are analysed using intention-to-treat (ITT) analyses.

The primary endpoint is the decrease in depressive symptoms in the BDI-II (Delta BDI-II) between study entrance (T1) and the end of the intervention (T3). A one-way ANOVA (within factor “group”) is performed to analyse the differences in the decrease of depressive symptoms between the intervention groups. A Bonferroni correction for multiple testing is applied to examine the expected group differences. This correction is carried out using the formula *α*/*n* (with alpha level *α* = 0.05 and *n* = number of tests) in order to lower the level of significance, make fewer results significant and thus the number of false-positive results reduce.

In an exploratory analysis, the basic effectiveness of the intervention compared to the control condition is examined (accompanied and unaccompanied group vs. control group) in order to counter the high drop-out rate.

In addition, the mean values including confidence intervals (95%) are recorded. The data are aggregated in the form of mean values and standard deviations. No interim analyses are planned.

To check the data obtained from the measuring instruments for normal distribution, the Kolmogorov-Smirnov test is calculated at the beginning. For this purpose, the mean values and standard deviations of each variable, as well as the Kolmogorov-Smirnov *Z*-value, are calculated, and the asymptotic significance (two-sided) is determined. Values below 0.05 indicate a violation of the normal distribution.

The intermediate measurements are analysed with regard to continuous outcome measures using repeated-measure ANOVAs. Independent *t* tests and *χ*^2^ tests are used to estimate the intergroup differences in sample characteristics prior to treatment.

Missing values in the data are replaced by multiple imputations, as well as “last-observation-carried-forward” (LOCF), “baseline-observation-carried-forward” (BOCF) and a “reference-based multiple imputation” method (“jump-to-reference” approach) to replace the missing values.

Effect size calculations to measure the therapeutic success (before and after the intervention) are carried out by dividing the difference between the respective group mean values by their pooled standard deviation.

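### The stated 200 subjects (400 after drop-out) do not give 80% power at d = 0.23 for the planned comparisons

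*Protocol article*

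**What the plan says.** In the protocol article, Sample size, the effect has a clear origin: "The between-group effect size estimate is based on meta-analytic evidence for the effect size observed in unaccompanied psychological interventions", given as d = 0.28. It is then lowered: "We conservatively reduced the estimated effect size to *d* = 0.23". With that value the section states "a power of 0.80 and an alpha level of 0.05, we need a total of 200 subjects to address our hypotheses". Next comes attrition: "The sample size was further estimated based on an expected drop-out rate of 50" per cent, which takes the total to 400. The design is described as "resulting in a total of three study groups to which the subjects are randomly assigned in a ratio of 2:2:1", that is 160, 160 and 80. G-Power is named as the software. The test family, the sidedness and any pre-post correlation are not given.

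Main hypotheses sets out three contrasts on the BDI-II: each version against control, and unaccompanied against accompanied. Trial objectives adds: "The framework of the trial is superiority". Planned statistical analysis makes the T1 to T3 change in BDI-II the primary endpoint, tests it with a one-way ANOVA by group, and adds: "A Bonferroni correction for multiple testing is applied to examine the expected group differences". The divisor is described only as the number of tests.

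**The concern.** A standardised difference of 0.23 is small, and 200 subjects in three unequal groups is a small number with which to detect it. The four stated figures (d, power, alpha, N) do not look compatible under the analysis that the plan describes. The calculation also makes no visible allowance for the 2:2:1 split or the Bonferroni correction, and it gives no effect for the contrast between versions, although that is a main hypothesis.

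At stake is how a null result is read. A reader who trusts 80% power at d = 0.23 would take a non-significant result as evidence against an effect of that size. If the true power is far lower, such a result says little, above all for the unaccompanied version and for the dismantling question.

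**Working it through.** **Inputs.** d = 0.23, power 0.80, alpha 0.05, total 200, 50% drop-out, 400 randomised as 160/160/80 (all from Sample size). After 50% drop-out the groups are 80/80/40. Two-sided testing is assumed because the article does not say; one-sided results are shown as well. Results are from the noncentral t or noncentral F distribution unless marked as normal.

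**1. The plan's own figure.** The drop-out step is right: 200/(1 − 0.5) = 400, and 160 + 160 + 80 = 400. The 200 does not reproduce.

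- Two groups, 1:1, two-sided, normal: n per group = 2(1.960 + 0.842)²/0.23² = 2 × 7.849/0.0529 ≈ 297. Noncentral t gives 298, so 596 in total.
- The same, one-sided: 2(1.645 + 0.842)²/0.23² ≈ 234. Noncentral t gives 235, so 470 in total.
- Two groups, 2:1, two-sided: about 447 versus 224. In a 2:2:1 trial that means 5 × 224 = 1,120 completers.
- Three-group one-way ANOVA, equal groups, f = d/2 = 0.115: 732 in total.

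**2. Routes that do land near 200.**

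- Entering the value as Cohen's f in a three-group one-way ANOVA: f = 0.22 gives 203 and f = 0.23 gives 186. In two-group terms f = 0.23 is d = 0.46.
- A repeated-measures group-by-time interaction with f = 0.115, three groups and two time points: 259 at correlation 0.3, 204 at 0.45, 186 at 0.5.

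The first uses a different effect measure from the one stated. The second needs a correlation that the article does not give, and it is an omnibus formula rather than the stated primary test.

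**3. Power at d = 0.23.** The noncentrality is d/√(1/n₁ + 1/n₂). For 80 versus 40 it is 0.23/√(1/80 + 1/40) = 1.188, and Φ(1.188 − 1.960) = 0.22 (normal).

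| Contrast | n | Two-sided 0.05 | One-sided 0.05 | Two-sided 0.05/3 |
|---|---|---|---|---|
| Unaccompanied v control, 50% drop-out | 80 v 40 | 22% | 32% | 11% |
| Unaccompanied v control, all observed | 160 v 80 | 39% | 51% | 23% |
| Between versions, 50% drop-out (d assumed) | 80 v 80 | 30% | 42% | 17% |
| Between versions, all observed (d assumed) | 160 v 160 | 54% | 66% | 37% |

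The divisor 3 is an assumption, taken from the three contrasts in Main hypotheses.

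**4. Effect detectable with 80% power, two-sided.** By the normal formula d = 2.802 × √(1/n₁ + 1/n₂); for 80 versus 40 this is 2.802 × 0.1936 = 0.54. By noncentral t:

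| n | alpha 0.05 | alpha 0.05/3 |
|---|---|---|
| 80 v 40 | 0.55 | 0.63 |
| 160 v 80 | 0.39 | 0.45 |
| 80 v 80 | 0.45 | 0.52 |
| 160 v 160 | 0.31 | 0.36 |

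**The case against.** The strongest defence is that the article does not say which G-Power routine was used, and a repeated-measures interaction with the correct f = 0.115 and a moderate correlation does give about 200. The analysis section plans repeated-measures ANOVAs. This stands as a possible origin of the number, so a reader should not conclude that d was certainly mistaken for f; the article does not show either. It does not rescue the claim. Those repeated-measures analyses are for the intermediate measurements, the primary test is a one-way ANOVA on the change, and an omnibus interaction does not power the pairwise hypotheses.

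Three further points limit the size of the problem.

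- A reader might apply the 22% to both versions against control. The 0.23 comes from unaccompanied programmes, and the Background reports medium to large effects for accompanied ones. At d = 0.5, 80 versus 40 has about 73% power. The low figure belongs to unaccompanied versus control.
- A reader might treat 80/80/40 as the analysed sample. Planned statistical analysis specifies intention to treat with imputation, Intervention defines drop-out by three weeks without module work, and the section on crises and suicidality says that data collection from drop-outs will be attempted. The 50% case is therefore the low end, and the all-observed case belongs beside it.
- A reader might add that baseline-carried-forward or jump-to-reference imputation dilutes the effect. If it halved d to 0.115 with 160 versus 80 and an unchanged SD, power would be about 13%. The plan lists these methods with others and does not say which is primary, so this is one scenario and not a consequence of the plan.

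**Conclusion.** The power statement is wrong as written for the planned comparisons. At d = 0.23 the required total is about 470 to 732 in the standard equal-group variants, which is 2.3 to 3.7 times the stated 200 (470/200 = 2.35; 732/200 = 3.66). For unaccompanied versus control, the comparison from which d = 0.23 is drawn, power is 22% to 39% two-sided and 32% to 51% one-sided, before any Bonferroni correction. The 30% to 54% between versions is illustrative, because the plan assigns no effect to that contrast.

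The conclusion does not depend on sidedness, on the drop-out scenario or on the number of tests: none of these choices brings unaccompanied versus control near 80%. It does rest on taking d as a two-group standardised difference in the analysed change score, which is how the section introduces it. The documents do not establish how 200 was obtained. The allocation of 400 and the drop-out step are arithmetically correct.

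**What to change.** Keep N = 400 and replace the power sentence with what the design delivers. Suggested content:

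- With 400 randomised 2:2:1 and two-sided alpha 0.05, there is 80% power for d of about 0.55 (50% drop-out) to 0.39 (all observed) for each version versus control, and about 0.45 to 0.31 between versions.
- At d = 0.23, power for unaccompanied versus control is about 22% to 39%. For the contrast between versions, state the effect assumed and its power; at d = 0.23 this is about 30% to 54%.
- Give the matching figures at the Bonferroni-adjusted alpha, with the number of tests stated. With three tests, power at d = 0.23 is 11% to 23% and 17% to 37%.
- Name the test, the sidedness and, if a repeated-measures formula was used, the correlation.

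The cost is one rewritten paragraph. No patients, endpoints or tests change. The stated power becomes less favourable.

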Voluntary termination was handled according to the study programme. Researchers will go beyond the protocol to contact dropped-out participants and try to continue the collection of data.

In case of harm induced by the trial, even though this is unlikely as depicted above, there is insurance coverage for the study participants provided by Selfapy’s public liability insurance GmbH. There are no guidelines for stopping the study. The study design was approved by the ethics committee of the medical faculty of the Charité University Medicine Berlin.

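### Doubling 200 to 400 for 50% drop-out keeps the claimed 0.80 power only under random loss with matching imputation, or if d already counts drop-outs; it does not hold for every ITT analysis named

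*Protocol article*

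**What the plan says.** **Sample size section.** The effect size comes from meta-analytic evidence: "We conservatively reduced the estimated effect size to *d* = 0.23". With "a power of 0.80 and an alpha level of 0.05", the authors conclude that "we need a total of 200 subjects to address our hypotheses". They then write "The sample size was further estimated based on an expected drop-out rate of 50" per cent, the upper end of a cited range of 9% to 50%, and "Based on this assumption, we would need a total of 400 subjects". Allocation is 160 accompanied, 160 unaccompanied and 80 control.

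**Planned statistical analysis section.** "The treatment results of all subjects (pre-post difference) are analysed using intention-to-treat (ITT) analyses". The primary endpoint is the fall in BDI-II from T1 to T3. Missing values are handled by multiple imputation, LOCF, baseline carried forward (BOCF) and jump-to-reference. None is called the main method. No completer or per-protocol analysis is described.

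**Intervention section, below Table 1.** A subject counts as a drop-out after three weeks without working on the modules, judged from logins. This is a definition of stopping the programme, not of a missing BDI-II.

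**Responses to crises and suicidality section.** "Researchers will go beyond the protocol to contact dropped-out participants and try to continue the collection of data".

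**The concern.** Dividing by (1 − p) is the correction for lost information. It assumes that a drop-out adds nothing to the analysis and that the effect among those analysed is undiminished. The rest of the protocol allows two other outcomes.

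- A drop-out who is reached at T3 enters the ITT comparison with a real score, as a programme-arm member who used only part of the programme. If the benefit has gone, that person pulls the mean difference down.
- A drop-out who is not reached may be given no change (BOCF) or a control-like outcome (jump-to-reference). Both shrink the mean difference.

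Dilution is not repaired by 1/(1 − p). If outcomes are kept, drop-outs gain nothing and the SD is unchanged, the required N grows with 1/(1 − p)².

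At stake is how a null result is read. A non-significant ITT or jump-to-reference result could be taken as evidence against the programme at 80% power when the power for that analysis was much lower.

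**Working it through.** **Inputs from the protocol:** base N = 200, power 0.80, alpha 0.05, d = 0.23, drop-out p = 0.5, allocation 160/160/80.

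**Assumptions:** two-sided test, the same drop-out in every arm, drop-out unrelated to outcome, and no programme effect in drop-outs for the no-benefit cases. A real drop-out either has a T3 score or does not, so each case below applies the 50% in one way only.

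**1. The plan's figure.** 200/(1 − 0.5) = 400. It reproduces exactly. The 200 is taken as given here. It does not follow from d = 0.23 (a 1:1 two-sided comparison of two means needs 594), but that is a separate matter.

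**2. Power relative to the base.** For 80% power the noncentrality is 1.96 + 0.84 = 2.80, and it is proportional to effect × √N. Power ≈ Φ(noncentrality − 1.96).

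- *Missing-at-random multiple imputation.* The information is about that of the 200 observed, so the noncentrality stays at 2.80 and power at about 80%.
- *Outcomes recovered, no residual benefit, d a completer effect.* The effect halves and N doubles: 2.80 × 0.5 × √2 = 1.98, power 51%. The N needed would be 200/(0.5)² = 800.
- *Jump-to-reference.* The effect halves and the Rubin's-rules standard error is about that of 200 observed: 2.80 × 0.5 = 1.40, power 29%.
- *BOCF.* Let m be mean change divided by SD of change. The effect halves, but the variance becomes 0.5 + 0.25m², so the N equivalent to 200 is 200 × 4 × (0.5 + 0.25m²) = 400 + 200m². The protocol does not give m.

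| m (assumed) | Equivalent N | Noncentrality at 400 | Power |
|---|---|---|---|
| 0 | 400 | 2.80 | 80% |
| 0.5 | 450 | 2.64 | 75% |
| 1.0 | 600 | 2.29 | 63% |
| 1.5 | 850 | 1.92 | 48% |

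**3. Checks.**

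- Simulation of 160 v 80 used 50% random missingness, 20 imputations, 3,000 replicates, a control change of 0.6 or 0.3 SD, and d = 0.543, set so that 80 v 40 has about 80% power. It gave: completers 78 to 79%, missing-at-random imputation 77%, BOCF 62 to 71%, recovered without benefit 49 to 50%, jump-to-reference 23 to 25%. The last lies below the analytic 29% partly because the Rubin's-rules standard error overstates the sampling error of a jump-to-reference estimate.
- A three-group ANOVA, reading 0.23 as f (the most favourable reading), starts at 0.83 with N = 200. At N = 400 it gives 0.52 with the effect halved. With jump-to-reference it gives 0.28. BOCF gives 0.83, 0.79, 0.66 and 0.50 at m = 0, 0.5, 1.0 and 1.5.

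**4. Break-even.** 400 analysed match 200 completers only if the ITT set keeps at least √0.5 = 71% of the standardised effect.

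**5. Dependence on the rate.** At the cited 9%, 200/0.91 = 220 and 200/0.91² = 242. The gap matters because p is 50%.

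**6. Scale at the protocol's own d.** Two-sided 0.05, before Bonferroni. For one arm v control with all analysed, the SE is √(1/160 + 1/80) = 0.137 and 0.23/0.137 = 1.68, so power is Φ(−0.28) = 0.39. The other cells follow in the same way.

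| Comparison | All randomised, d = 0.23 | Half of each arm, d = 0.23 | All randomised, d = 0.115 |
|---|---|---|---|
| One arm v control | 0.39 | 0.22 | 0.13 |
| Accompanied v unaccompanied | 0.54 | 0.31 | 0.18 |

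**The case against.** The strongest reply is that 1/(1 − p) is a standard allowance for lost outcomes and is compatible with ITT. Multiple imputation is listed first, and under a missing-at-random model it leaves power where the completer calculation put it. BOCF and jump-to-reference can be read as sensitivity analyses, and a trial need not be powered for its most conservative one. Ranking the methods may properly sit in an analysis plan that is not shown. The login rule cannot apply to controls, who have no programme access, yet the inflation covers them too. That suggests the 50% was meant as ordinary loss of outcome data. Finally, if d = 0.23 already includes drop-outs, multiplying it by (1 − p) counts dilution twice.

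Most of this stands, and it rules out the stronger readings that a reader might infer:

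- *That the step is an arithmetic error.* It is not; the division is correct.
- *That the plan gives all drop-outs no benefit.* Only BOCF and jump-to-reference do so. LOCF can carry a T2 improvement forward.
- *That the 0.80 rests wholly on a completer set nobody will analyse.* Missing-at-random imputation on all subjects supports the same figure.
- *That 800 are needed.* That requires a completer d, full recovery of outcomes and zero residual benefit. A subject inactive for three weeks may already have completed many modules.

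What the reply does not answer is that the protocol states one power figure without tying it to a method or to a kind of effect. Its own drop-out definition and follow-up effort also make dilution a live possibility. The jump-to-reference loss remains even if d is an all-randomised effect.

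**Conclusion.** The concern holds in a limited form. The 400 is consistent with 0.80 if drop-outs are lost at random and imputed under missing at random, or if their outcomes are already reflected in d. It is not consistent with 0.80 across the ITT analyses that the protocol names. From about 80% in completers with 50% random drop-out, power is:

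- about unchanged under missing-at-random imputation;
- about 50% with recovered outcomes, if drop-outs keep no benefit and d is a completer effect;
- about 25 to 29% under jump-to-reference;
- between no loss and roughly 48% under BOCF, for m from 0 to 1.5.

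These are losses relative to an assumed sound base. At d = 0.23, power for one arm v control is low even before any dilution (0.39 with everyone analysed). A missed effect at that d should therefore not be blamed on the inflation step alone. Confidence is moderate, because the protocol does not say which kind of effect d is, what share of drop-outs will lack a T3 score, or the mean change relative to its SD.

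**What to change.** Keep 400 as the enrolment. In the Sample size section:

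1. State whether d = 0.23 is an effect in all randomised subjects or in completers. Scale it by the retained share of the effect only if it is a completer effect.
2. Replace the single 0.80 with the power that 160/160/80 gives for the planned ITT comparisons, naming the main imputation method to which it applies and allowing for Bonferroni.
3. Show the power under jump-to-reference as the lower bound.

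The cost is a few sentences and a short calculation; recruitment is unaffected. The downside is that the stated power becomes less favourable.

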### Planned statistical analysis

The recorded data of the different measurement times (T1, T2, T3 and T4) for both intervention groups and the control group are analysed. The treatment results of all subjects (pre-post difference) are analysed using intention-to-treat (ITT) analyses.

The primary endpoint is the decrease in depressive symptoms in the BDI-II (Delta BDI-II) between study entrance (T1) and the end of the intervention (T3). A one-way ANOVA (within factor “group”) is performed to analyse the differences in the decrease of depressive symptoms between the intervention groups. A Bonferroni correction for multiple testing is applied to examine the expected group differences. This correction is carried out using the formula *α*/*n* (with alpha level *α* = 0.05 and *n* = number of tests) in order to lower the level of significance, make fewer results significant and thus the number of false-positive results reduce.

In an exploratory analysis, the basic effectiveness of the intervention compared to the control condition is examined (accompanied and unaccompanied group vs. control group) in order to counter the high drop-out rate.

In addition, the mean values including confidence intervals (95%) are recorded. The data are aggregated in the form of mean values and standard deviations. No interim analyses are planned.

To check the data obtained from the measuring instruments for normal distribution, the Kolmogorov-Smirnov test is calculated at the beginning. For this purpose, the mean values and standard deviations of each variable, as well as the Kolmogorov-Smirnov *Z*-value, are calculated, and the asymptotic significance (two-sided) is determined. Values below 0.05 indicate a violation of the normal distribution.

The intermediate measurements are analysed with regard to continuous outcome measures using repeated-measure ANOVAs. Independent *t* tests and *χ*^2^ tests are used to estimate the intergroup differences in sample characteristics prior to treatment.

Missing values in the data are replaced by multiple imputations, as well as “last-observation-carried-forward” (LOCF), “baseline-observation-carried-forward” (BOCF) and a “reference-based multiple imputation” method (“jump-to-reference” approach) to replace the missing values.

Effect size calculations to measure the therapeutic success (before and after the intervention) are carried out by dividing the difference between the respective group mean values by their pooled standard deviation.

Effect sizes under 0.2 are deemed small, and 0.5 moderate and 0.8 are deemed large [36].

All data evaluations are carried out without knowledge of the political group affiliation (blinded data evaluation). That means the evaluating person does not know which expression of the group variable indicates the representation to the IG and which the rights to the KG.

An external team was built, in order to monitor and recheck the execution of the planned statistical analysis.

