### Accompanied group

In the accompanied version of the programme, the subjects are supervised by experienced psychotherapists in training throughout the duration of the programme. In the beginning, the expert and the subject get to know each other and consequently hold 20- to 25-min conversations by phone on a weekly basis. In the course of this conversation, the psychotherapists address the content from Table 1 in a structured manner. A special focus lies on discussing and reviewing the accomplishment of the exercises incorporated in each module*.* In a 1-h training session, all clinical psychologists who were interested in accompanying subjects were informed. The training included general information on the study, risks and handling of these risks, a discussion of the non-accident concept, instructions on the handling and documentation of drop-outs and information on the standardization of the discussion content.

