### Responses to crises and suicidality

A physical overuse can be excluded. The online survey at the time of measurement T1, T3 and T4 of the survey will take about 60 min (Table 2). The processing time for T2 is about 30 min. A general side effect of the interventions could possibly be a lack of treatment success. The most severe adverse event that could happen is acute suicidality. Suicidality is monitored using the BDI-II (after 6, 12 and 24 weeks) and the HRSD-24 (after 12 and 24 weeks). In case of a score of 3 (suicidal thoughts or behaviour) on item 3 on the HRSD-24 or in case of a score of 2 (suicidal thoughts or wishes) on item 9 of the BDI-II, discontinuation will be initiated. Each rater has an emergency plan, and the respective participant will be shifted to inpatient or outpatient psychotherapy.

**Table 2 Tab2:** Assessment tools utilized throughout the programme

Assessment timeframe	Assessment instrument
Pre (T1)	Self-assessment—questionnaires: BDI-II; QIDS-SR16; BAI; WHOQOL-BREF; SWOP-K9; WAI-SR; APOI; SASS; Bado
	Assessment by a therapist – Questionnaires: MINI; HRSD-24
During (T2)	Self-assessment—questionnaires: BDI-II; QIDS-SR16; BAI; WAI-SR; APOI
Post (T3)	Self-assessment—questionnaires: BDI-II; QIDS-SR16; BAI; WHOQOL-BREF; SWOP-K9; WAI-SR; APOI; SASS; Bado Assessment by a therapist—questionnaire: HRSD-24
Follow-up (T4)	Self-assessment—questionnaires: BDI-II; QIDS-SR16; WHOQOL-BREF; Bado Assessment by a therapist—questionnaire: HRSD-24

*Abbreviations*: *MINI*, Mini International Neuropsychiatric Interview; *BDI-II*, Beck Depression Inventory-II; *QIDS-SR16*, Quick Inventory of Depressive Symptomatology; *BAI*, Beck Anxiety Inventory; *WHOQOL-BREF*, WHO Quality of Life-BREF; *SWOP-K9*, Self-Efficacy, Optimism, and Pessimism Scale; *WAI-SR*, Working Alliance Inventory - Short Revised; *APOI*, Attitudes towards Psychological Online Interventions Questionnaire; *Bado*, basic documentation; *HRSD-24*, Hamilton Depression Scale; *SASS*, Social Activity Self-Assessment Scale

Subjects are allowed to attend ongoing psychotherapy. This reflects everyday treatment and ensures high external validity. Furthermore, it limits potential negative consequences due to the lack of treatment success, as additional treatment can be accessed, when needed. All potentially relevant factors for treatment outcome are taken into account for the statistical evaluation.

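### The primary test is a one-way ANOVA on raw BDI-II change with no covariate: valid under randomisation, but less precise than adjusting for the baseline score the trial already collects

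*Protocol article*

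**What the plan says.** Under Planned statistical analysis, the primary endpoint is the BDI-II decrease from study entrance (T1) to the end of the intervention (T3). The test is given as: "A one-way ANOVA (within factor “group”) is performed to analyse the differences in the decrease of depressive symptoms between the intervention groups". The section names no covariate and no therapist term in this or any other analysis. Baseline characteristics are only compared between groups by t and chi-square tests, which adjusts nothing.

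Under Responses to crises and suicidality, the article states "Subjects are allowed to attend ongoing psychotherapy", and shortly afterwards: "All potentially relevant factors for treatment outcome are taken into account for the statistical evaluation". Table 2 in that section shows the BDI-II and the Bado sheet collected at T1.

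Under Accompanied group, "the subjects are supervised by experienced psychotherapists in training throughout the duration of the programme", and they "hold 20- to 25-min conversations by phone on a weekly basis".

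**The concern.** A change score uses the baseline with its coefficient fixed at 1. Unless the T1–T3 correlation is close to 1, that is not the efficient weight, and the between-group comparison carries more noise than it needs to. A chance difference between arms at T1 also passes partly into the estimate. This matters most in the contrasts with the control arm, which has 80 subjects, or about 40 after the expected drop-out.

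The statement that all relevant factors are accounted for has no counterpart in the named analyses. A reader cannot tell which factors are meant, or whether they are measured before or after randomisation.

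The ANOVA also treats subjects as independent. If accompanied subjects share therapists, the standard error of the two contrasts that involve that arm may be too small.

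**Working it through.** **Inputs from the article.** Effect size d = 0.23, alpha 0.05, 50% drop-out, and arms of 160 accompanied, 160 unaccompanied and 80 control (Sample size). Halving gives 80, 80 and 40.

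**Inputs assumed.** The T1–T3 correlation rho is not given; 0.3 to 0.8 is used. The article does not say in which SD d is expressed; post-score SD is used. Tests are two-sided at 0.05 without the planned Bonferroni correction, because the number of tests is not stated.

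**The plan's own figure.** The drop-out step reproduces: 200/(1 − 0.5) = 400. The 200 itself does not follow from d = 0.23, power 0.80 and alpha 0.05: a two-sided 1:1 two-sample test needs 594. That is a separate matter. Only d and the arm sizes are used below.

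**Variance.** With common SD s at T1 and T3:

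- change score: 2(1 − rho)s²
- baseline-adjusted: (1 − rho²)s²
- ratio: (1 − rho²)/[2(1 − rho)] = (1 + rho)/2

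This gives 0.65 at rho 0.3, 0.75 at 0.5, 0.80 at 0.6 and 0.90 at 0.8, which is 35% to 10% fewer subjects for the same power.

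**Power** (noncentral t). The standardised effect is 0.23/√[2(1 − rho)] for change and 0.23/√(1 − rho²) after adjustment. At rho 0.5 these are 0.230 and 0.266.

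| rho | 160 v 80 | 80 v 40 | 160 v 160 |
|---|---|---|---|
| 0.3 | 29% to 42% | 17% to 23% | 41% to 58% |
| 0.5 | 39% to 49% | 22% to 27% | 54% to 66% |
| 0.6 | 46% to 55% | 26% to 31% | 63% to 73% |
| 0.8 | 75% to 80% | 46% to 50% | 90% to 93% |

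Each cell runs from change score to adjusted. The 80% in the first column is 79.6%.

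**Chance imbalance.** Given a T1 difference D between arms, the change-score contrast is shifted by (1 − rho)D. For 160 v 80 the standard error of D is √(1/160 + 1/80) = 0.137 SD. At rho 0.5, an imbalance of one standard error shifts the contrast by 0.5 × 0.137 = 0.068 SD, about 30% of 0.23 (0.068/0.23). Adjustment removes this. The shift averages zero over randomisations.

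**Shared therapists.** Neither caseload m nor intraclass correlation (ICC) is given; m = 8 to 16 and ICC = 0.02 to 0.05 are assumed. The design effect in the accompanied arm is DE = 1 + (m − 1)ICC. For equal arms the true variance is (DE + 1)/2 times the assumed one, and the true error of a nominal 5% test is 2[1 − Φ(1.96/√ratio)].

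- m = 8, ICC 0.02: DE 1.14, ratio 1.07, error 5.8%
- m = 16, ICC 0.05: DE 1.75, ratio 1.375, error 9.5%

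These are for accompanied v unaccompanied. For accompanied v control (160 v 80) the same inputs give ratios of 1.047 and 1.25, and errors of 5.5% and 8.0%. The unaccompanied v control contrast is not affected by this calculation.

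**The case against.** The strongest reply is that nothing here invalidates the primary test, and that stands. A reader might infer that the baseline score is thrown away or the estimate biased. The documents do not support that: the change score does use T1, and under randomisation its contrast is unbiased. Nor does the BDI-II entry threshold create bias between arms, since it applies to everyone before allocation and regression to the mean cancels in expectation.

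A reader might also see a flat contradiction between the ANOVA and the statement on relevant factors, or a plan to adjust for treatment begun after randomisation. Neither is shown. The statement concerns the evaluation in general, an adjusted secondary analysis could honour it, and a condensed article may leave the covariate list to a fuller document. What remains is that the model the article does fix contains none of these factors.

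Calling group a within factor is a wording slip: a one-way ANOVA of change by allocated arm can only be between subjects. The repeated-measures ANOVAs serve the intermediate measurements, and the same section plans imputation, so loss of subjects with a missed visit is not established.

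Clustering is the least certain part. With 160 accompanied subjects and weekly calls, shared therapists are a fair inference. The article gives no number of therapists, caseload or ICC, and its structured calls and standardised discussion content may limit differences between therapists. The mention under Engagement and usage measures for iCBT of "correspondence shared between a subject and his/her respective therapist" concerns log files and does not show sharing. It would go too far to say that the standard error is understated; it may be.

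**Conclusion.** The point holds as a loss of precision that can be recovered, not as an error of inference. The fixed primary model is unadjusted, and adjusting for T1 BDI-II would cut the variance to 0.65–0.90 of its present value for an assumed rho of 0.3 to 0.8. The gain shrinks as rho rises.

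It does not rescue the trial's power. At rho 0.5 every contrast stays below 80%, and the contrasts with control stay below 80% over the whole assumed range. Only 160 v 160 at high rho exceeds it, with all randomised subjects counted and no Bonferroni correction.

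The true error of about 6% to 9.5% for accompanied v unaccompanied rests wholly on the assumed caseload and ICC. It justifies a sensitivity analysis and no more.

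**What to change.** Make the primary model an ANCOVA of T3 BDI-II on three-level group with T1 BDI-II as covariate. Using the T1–T3 change as outcome with the same covariate gives the same group contrasts, so the stated endpoint can stay. The equivalent mixed model over T2 to T4, with T1 as covariate and the T3 contrast as primary, is an alternative.

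List in advance any further factors meant by the general statement, and limit them to ones measured before randomisation, for example ongoing psychotherapy at T1 from the Bado sheet. Baseline antidepressant use should be listed only if its collection is confirmed, since the article's description of the sheet does not mention medication.

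As a sensitivity analysis, if therapist identity is recorded, add a therapist random effect in the accompanied arm only.

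The cost is analysis wording. T1 BDI-II is already collected, and no design change is needed. The therapist term costs a few degrees of freedom, and the availability of a therapist identifier has to be checked first.
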